10.7.4 Sample size

We will use all 2,813 enrollees where possible, and for other analyses, the 2,259 randomized subjects. For continuous outcome measures, we will have 90% power to detect a difference of 0.09 SD at baseline, and 0.11 SD at year 2, based on t-tests comparing allocation beliefs. For multivariable analyses, assuming that each additional predictor variables requires a 10% increase in sample size, we will be able to detect adjusted differences of 0.15 SD at baseline and 0.20 SD at Year 2 or EOT in models containing 20 additional predictors. For binary outcomes, at baseline, we will have 90% power to detect an odds ratio <1.3 at baseline, year 2 and EOT. For multivariable analyses assuming the outcome has prevalence of just 10% of the total sample, model estimates will be reliable with 28 predictors for baseline data models and 16 predictors for year 2 models. Hence our study sample is sufficient for the analyses described.

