# 3. Assess the effects of allocation beliefs, efficacy beliefs, and preference on adherence.

*10.7.3 Data collection*

Data collection (approved previously) is conducted as part of the routine interviews for the parent study, as well as separate mail-back study methods surveys.

*10.7.4 Analyses*

Allocation beliefs will be classified as “Believe Active” (A) for any active treatment option in the 4-arm study or calcium+vitamin D in the 2-arm study;. “Believe Placebo” (P) for placebo in the 4-arm study; calcium in the 2-arm study; or “Don’t Know (DK). We will analyze all subjects, and separately those in the 4-arm and 2-arm studies. We will assess the distribution of forced guesses of those who said DK and incorporate the appropriate analyses and sensitivity analyses to show the effect of pooling forced guesses with Active or Placebo guesses. A 2-sided p-value <0.05 will be considered statistically significant. We will not adjust for multiple testing. Our analyses will be based primarily on describing the data and regression modeling..

Aim 1. Identify predictors of allocation belief at randomization, year 2, and EOT.

At different times during the trial, we will classify the reasons subjects provided for their allocation beliefs and explore the factors that predict beliefs. We will explore the factors associated with misunderstanding of equipoise and randomization.

Hypothesis 1. Allocation beliefs change during the course of a double-blinded trial. We will describe the distributions of beliefs, changes in beliefs from randomization to year 2 [EOT], and use regression models to identify factors related to changes of belief.

Aim 2. Examine how subjective and objective health outcomes are affected by allocation beliefs, efficacy beliefs, and preference.We will assess how beliefs affect subsequent symptoms and on colorectal adenoma, using multivariable regression.

Hypothesis 2a. Allocation beliefs at randomization [year 2, EOT] predict the occurrence of each of five specified health effects, after adjustment for a history of that same health effect. We will use multivariable regression models of the relations between beliefs and subsequent symptoms identified during routine bi-annual telephone surveys.

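### The beliefs-and-bias study's detectable differences (0.09/0.11 SD; 0.15/0.20 SD adjusted) are reached only if the total sample is taken as the size of each group, and the odds-ratio claim fails at year 2 and end of treatment

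*Protocol*

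**What the plan says.** Section 10.7.4 (Sample size) gives the available numbers as totals: "We will use all 2,813 enrollees where possible, and for other analyses, the 2,259 randomized subjects". For continuous outcomes it claims "we will have 90% power to detect a difference of 0.09 SD at baseline, and 0.11 SD at year 2". The method named for this figure is a two-group comparison: "based on t-tests comparing allocation beliefs". It then inflates the required sample by 10% for each extra predictor and states that, with 20 predictors, "we will be able to detect adjusted differences of 0.15 SD at baseline and 0.20 SD at Year 2 or EOT". For binary outcomes it says "we will have 90% power to detect an odds ratio <1.3 at baseline, year 2 and EOT", without naming an outcome prevalence. It adds that, at 10% prevalence, models could carry 28 predictors at baseline and 16 at year 2. From these figures it concludes that the sample is sufficient.

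The preceding Analyses section (also numbered 10.7.4) fixes the test level: "A 2-sided p-value <0.05 will be considered statistically significant". It also defines the groups: "Allocation beliefs will be classified as “Believe Active” (A) for any active treatment option in the 4-arm study", against Believe Placebo, with a third class for Don't Know. No expected split between the classes is given.

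**The concern.** The people compared in the t-test are the same 2,813 or 2,259 people, sorted by what they believe they were given. The total therefore has to be shared between at least two groups, and the stated differences look too small for that.

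The sub-study asks whether participants' beliefs shift symptoms, SF-36 scores and adherence. A null result is informative only relative to the effect the study could have detected. If that effect is understated, an absence of belief-related bias will be claimed with more confidence than the data support.

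**Working it through.** **Inputs.** Totals of 2,813 (baseline) and 2,259 (randomized, so the ceiling for year 2 and end of treatment), 90% power, the t-test and the 10%-per-predictor rule come from section 10.7.4 (Sample size). Two-sided 0.05 comes from section 10.7.4 (Analyses). Assumed, because not stated: a 1:1 split with nobody in Don't Know, which is the best case.

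**Year-2 sample size.** None is given. Ten events per predictor at 10% prevalence turns 2,813 into 0.10 × 2,813 / 10 = 28 predictors, which is the stated baseline count. The same rule turns the stated 16 predictors into 16 × 10 / 0.10 = 1,600 subjects. The rule is inferred, so year-2 results are shown for both 2,259 and 1,600.

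**Formula.** Detectable difference in SD units: d = (1.960 + 1.282) × √(1/n₁ + 1/n₂) = 3.242 × √(1/n₁ + 1/n₂). With 20 predictors the required sample rises by a factor 1 + 20 × 0.10 = 3, so the adjusted d is √3 × d.

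**Reproducing the stated figures.** Enter the total as the size of each group, d = 3.242 × √(2/N):

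| N entered per group | d | d × √3 | Stated |
|---|---|---|---|
| 2,813 | 0.086 | 0.150 | 0.09 and 0.15 |
| 1,600 | 0.115 | 0.199 | 0.11 and 0.20 |
| 2,259 | 0.097 | 0.167 | (no match) |

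All four stated values appear, from one slip.

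**Correct calculation.** Split the total in two, d = 3.242 × 2/√N. The last column is the power at the stated unadjusted and adjusted differences:

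| Total N | d | d × √3 | Power at stated differences |
|---|---|---|---|
| 2,813 (baseline) | 0.122 | 0.212 | 67% at 0.09; 63% at adjusted 0.15 |
| 2,259 (year 2, ceiling) | 0.136 | 0.236 | 74% at 0.11; 78% at adjusted 0.20 |
| 1,600 (year 2, implied) | 0.162 | 0.281 | 59% at 0.11; 64% at adjusted 0.20 |

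**Subjects needed for the stated differences.** For 0.09 SD: 2,595 per group, 5,190 in total (4,658 even if 0.09 were rounded down from 0.095), against 2,813 enrolled. For 0.11 SD: 1,737 per group, 3,474 in total (3,180 even at 0.115), against 2,259 randomized. This step does not use the inferred 1,600.

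**Other readings tried, with the total split.**
- Two-sided with 80% power gives 0.106 SD at baseline.
- One-sided with 90% power gives 0.110 SD at baseline.
- One-sided with 80% power gives 0.094 SD at baseline, but contradicts the stated power and sidedness and gives 0.162 adjusted (0.0938 × √3), not 0.15.
- Unequal groups are worse: a 70/30 split gives 3.242 × √(1/0.7N + 1/0.3N) = 0.133 SD for N = 2,813 and 0.177 SD for N = 1,600.

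**Odds ratio.** Smallest odds ratio detectable with 90% power, total split 1:1, from a two-proportion power calculation. At 50% prevalence the Wald approximation exp(3.242 × 4/√N) agrees: 1.277, 1.314 and 1.383. The best case lies near 46% to 47% prevalence.

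| Total N | Best case | 30% prevalence | 10% prevalence | Best-case power at OR 1.3 |
|---|---|---|---|---|
| 2,813 | 1.28 | 1.30 | 1.46 | 93.5% |
| 2,259 | 1.31 | 1.34 | 1.52 | 87.6% |
| 1,600 | 1.38 | 1.41 | 1.64 | 74.6% |

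**The case against.** The core SD figures cannot be rescued, but several points on the other side deserve weight.

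- **The √2 factor at year 2 depends on an inferred sample size.** Against 2,259, the shortfall is 0.136 versus 0.11 (24%) unadjusted and 0.236 versus 0.20 (18%) adjusted. This is correct, so year-2 results are given as a range. It does not save the claim, because 0.11 SD needs more subjects than were randomized.
- **The odds-ratio miss is small if all 2,259 contribute.** It is 1.31 against 1.3, with power of 87.6% against 90%. That is fair; the failure is clear only near 1,600. Still, the text promises 90% power at year 2 and end of treatment, and no prevalence delivers it.
- **The 10% prevalence is not attached to the odds-ratio sentence.** True; it belongs to the statement on predictor counts. The 10% column shows how strongly the claim depends on an unstated input and is not a contradiction in itself. The 70/30 split is likewise only an illustration.
- **Little depends on these numbers.** The sub-study uses data already collected, the parent trial fixes its size, and null results can be judged from confidence intervals. No minimum important difference is named, so 0.12 to 0.28 SD is not shown to be inadequate. This limits the consequence. It does not make the stated power correct, and the paragraph's conclusion of sufficiency rests on it.

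**Conclusion.** The concern holds. The four SD figures are not attainable with the stated totals, power and two-sided test. They correspond to using the total sample as the size of each group, which understates the detectable difference by √2, about 40%, at baseline and, if about 1,600 contribute, at year 2. If all 2,259 contribute, the year-2 shortfall is 24% unadjusted and 18% adjusted. The results assume equal belief groups and no Don't Know answers; relaxing either makes sensitivity worse. The odds-ratio claim is supportable at baseline for near-equal groups and prevalence of about 30% to 50%, but not at year 2 or end of treatment. The error concerns the interpretation of an ancillary study only.

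**What to change.** Restate the paragraph for two groups that share the total:

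- Unadjusted, equal groups: 0.12 SD at baseline and 0.14 to 0.16 SD at year 2.
- With 20 predictors: 0.21 SD at baseline and 0.24 to 0.28 SD at year 2 or end of treatment.
- Odds ratio: about 1.3 at baseline for outcomes of about 30% to 50% prevalence; at year 2 and end of treatment, 1.31 to 1.38 at best; at 10% prevalence, about 1.5 at baseline and 1.5 to 1.6 at year 2.

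State the year-2 and end-of-treatment sample size so that each range becomes a single figure. Also state the assumed split between belief groups, including Don't Know, and the prevalence behind the odds ratio. Rest the conclusion that the sample is sufficient on the corrected figures. The cost is a text change; design, data collection and the planned analyses stay as they are.

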10.7.5 Additional Risks

This sub-study presents no additional physical risk to the subjects. Confidentiality of data is well protected, as described earlier.

10.7.6 Benefits and importance of knowledge to be gained

There is no direct benefit to subjects. Our results may improve randomized controlled trial methodology; in that case, society will benefit from improved trials in the future.

10.7.7 Inclusion of women, minorities

The sub-study uses data from all subjects in the parent study.

10.8 Colds and Flu study

This ancillary study is under the direction of [name], PI for the parent study at the Geisel School of Medicine at Dartmouth.

10.8.1 Background and rationale

Observational studies indicate that vitamin D may play a role in the prevention of infectious diseases. We will evaluate the effects of vitamin D supplementation on the incidence and duration of upper respiratory tract infection (URTI), influenza-like illness (ILI), and acute gastrointestinal illness (AGI), by adding surveillance for these three illnesses to our on-going randomized controlled clinical trial of vitamin D and/or calcium supplementation for the prevention of colorectal adenomas.

10.8.2 Objectives

Our specific aims are:

To collect health dairies recording the incidence and duration of common infectious illnesses in approximately 800 subjects enrolled in our clinical trial of vitamin D and calcium.

To assess the effects of vitamin D supplementation on the risk of upper respiratory tract infections and explore effects on gastrointestinal illnesses, using formal standardized case definitions of URTI, ILI, and AGI

Our primary hypotheses are:

Supplementation with vitamin D3 (1000 IU/day) reduces the number of winter episodes of URTI.

Supplementation with vitamin D3 (1000 IU/day) reduces the number of winter days affected by URTI.

Our exploratory hypotheses are:

Supplementation with vitamin D3 (1000 IU/day) reduces the number of episodes of URTI over a year of observation.

Supplementation with vitamin D3 (1000 IU/day) reduces both the number of winter episodes of ILI and the number of winter days affected by that illness.

Supplementation with vitamin D3 (1000 IU/day) reduces both the number of episodes of AGI and the days affected by that illness.

In addition, we will (i) compare the recent reporting of colds and ILI by subjects telephoned every 6 months among those randomized to vitamin D3 (1000 IU/day) supplementation or placebo; and (ii) examine the impact of serum levels of 25-hydroxyvitamin D3 (25-OHD) on subject’s experience of symptoms during the study.

10.8.3 Data collection

Questionnaires (implied consent) were administered as described in Section 6.2.

25-OHD was measured as described in Sections 5.12 and 9.1 - 9.3.

10.8.4 Analyses

URTI: We define a common cold or upper respiratory tract infection (URTI) as the presence of 2 or more of the following: runny nose, nasal congestion, sneezing, sore throat, cough, swollen or tender neck glands.

ILI: We define Influenza-like illness (ILI) as fever, plus 2 or more of the following: sore throat, cough, muscle ache, headache.

AGI: We will base our definition of acute gastrointestinal illness on Payment’s “highly credible gastrointestinal illness”: either 1) vomiting or watery diarrhea; or 2) nausea or soft diarrhea with abdominal cramps.

Further, our definition of an episode of illness requires 6 symptom-free days before a subsequent episode will be said to have occurred. We will require this symptom-free interval because we assume that symptoms occurring toward the end of an illness may not necessarily fulfill the case definition but will still be part of the episode. For example, on days 1, 2 and 3, a participant’s symptoms fulfill the definition of a common cold (sore throat and nasal congestion). On days 4 and 5 only a mild sore throat persisted, but the nasal congestion recurred on days 6 and 7, which together with the sore throat fulfill the case definition for those two days. According to our definitions, this constitutes only one episode of URTI. For the purposes of estimating “days of illness”, we will use our case definitions strictly, so that day 4 and 5 are excluded, and there were only 5 days of URTI altogether.

Statistical methods

Primary end points will be the number of episodes of each type of illness and the total number of days of affected by the illness. Because of the seasonally low vitamin D levels in winter, our main hypothesis is that supplementation will have an effect during those months, rather than during the summer.

For the analysis of the number of illness episodes, we will use Poisson regression to estimate the effect of treatment assignment to vitamin D. The primary analyses will be by intention-to-treat – i.e. we will ignore subject compliance in the analysis, which will be based solely on the randomized assignment. We adjust for calcium treatment assignment in all analyses. We will also pay special attention to over-dispersion or under-dispersion, as assessed by the usual chi-squared testing. If this is statistically significant, we will use robust methods to estimate standard errors and recalculate the confidence interval for the treatment effect. Other analyses e.g. of the days affected by illness will proceed in the same spirit.

We will compare randomized treatment groups in relation to the probability of any self reported health outcome ascertained during 6 monthly interviews (colds, ILI).

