***6.0 Post-randomization Follow-up***

The study coordinators at each Study Center will maintain regular contact with all subjects. Scheduled contacts with the subject are listed below. Some subjects, however, will be contacted more frequently to encourage adherence to treatment or to manage individual problems.

Follow-up activities once a subject is randomized will include:

- Every six months - interval questionnaire
- At years 1 and (where applicable) year 3 - laboratory measurements of calcium, creatinine, and vitamin D
- At Year 3 or Year 5 – follow-up colonoscopy, SF-36 Health Survey, End of Treatment Questionnaire, and laboratory measurement of vitamin D

All participants who complete Year 3 or Year 5 follow-up activities will be reimbursed $100 to defray the time and expense of these activities.

*6.1 Interval Questionnaires*

Every 6 months, all subjects will have a telephone interview regarding somatic symptoms possibly related to study agents, illnesses, doctor’s visits, hospitalizations, medications, over-the-counter preparations (including nutritional supplements), dietary intake of calcium and vitamin D, and compliance with study tablets. The responses to these questions will be entered by the study coordinator into a secure web-based form that transmits the data directly to the Dartmouth Project Coordination Center in real-time over the Internet. If access to the internet is interrupted or temporarily unavailable, a paper form will be used and the data will subsequently be entered into the web form. The interval questionnaire interview may also be performed in person when in conjunction with a Year 1 or Year 3 blood draw, as appropriate. If necessary (e.g., a subject is unavailable by phone or deaf), a subject may self-complete a paper questionnaire and return it to the study coordinator for data entry into the web form. Finally, subjects who have access to the internet will be able to self-complete the questionnaire on the web once that technology is available in the study. The interval questionnaire should be collected within 30 days on either side of each 6 month anniversary of the randomization date.

- 1. *Colds and Flu Questionnaires*

Subjects will be asked to complete up to eighteen monthly questionnaires distributed from the Dartmouth Project Coordination Center to collect information related to colds, flu and flu-like illnesses.

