A mailing will be sent to announce the availability of the web-based Questionnaire to all subjects who did not participate when only the paper questionnaire was available. This mailing will include:

- Cover letter
- Opt-In Postcard for subjects who did not participate when only the paper questionnaire was available.
- Instructions for completing web-based questionnaires

Reminders.

A reminder letter, e-mail or phone call will be generated from the Dartmouth Project Coordination Center or local study coordinator if an expected paper questionnaire is not returned or an online questionnaire not submitted.

Final mailing

We will continue to collect up to five additional questionnaires (not to exceed a total of eighteen) after the completion of the treatment phase because of the long half-life of vitamin D. Upon receipt of the final questionnaires, a letter will be sent with any remaining gift cards for questionnaires completed and submitted.

- 1. *Schedule of Lab Measurement*

Laboratory measurements at years 1, 3 and 5 will be used for safety and compliance purposes. The schedule of laboratory tests are summarized in the following table for subjects with either 3 or 5 year follow-up colonoscopies.

| Lab Measurement | Entry | Year 1 | Year 3 | Year 5 |
| --- | --- | --- | --- | --- |
| Calcium | XO | XO | O | - |
| Creatinine | XO | XO | O | - |
| 25-(OH)-vitamin D | XO | XO | XO | O |

Key: Subjects scheduled for colonoscopy follow-up exam at 3 years: X

Subjects scheduled for colonoscopy follow-up exam at 5 years: O

The interim blood draw(s) will be performed 1 year after randomization, as well as 3 years after randomization for subjects with a 5-year surveillance cycle. The interim blood draw(s) will be collected within 30 days prior to and 90 days after the randomization anniversary date. If the total calcium measurement is slightly elevated or slightly low, a re-test (of the original blood draw specimen) or a re-draw (draw for a new blood specimen), including an albumin measurement, will be used to estimate the ionized calcium level.

The final blood draw (year 3 or year 5) will be within the 60 days prior to the follow-up colonoscopy, while the subject is still taking the study pills, and, preferably, should not be performed at the colonoscopy exam (e.g. after the colonoscopy preparation has been administered to the subject).

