Colonoscopic visualization of the entire large bowel will be performed in each subject approximately 36 months or 60 months after the qualifying colonoscopy, as set out before randomization by each patient's clinician. This time frame (3 or 5 years) for colonoscopy surveillance following the qualifying examination is consistent with current clinical guidelines. Additional exams will not be encouraged unless required clinically; patients in whom more frequent exams are anticipated will not be randomized. Study coordinators will contact subjects by telephone or mail to remind them of their anticipated examination and to assist in scheduling, as possible. Study coordinators will contact subjects who do not return for examinations and attempt to persuade them to have their follow-up colonoscopy or determine why this is not possible. The specific timing of this follow up colonoscopy, which results in the end of the treatment phase of the study for this subject, will vary according to the circumstances of the individual subject and the scheduling procedures of the clinic and the patient’s clinician. Therefore, the window for this colonoscopy will be from 6 months prior to the 3 or 5 year anniversary of the qualifying colonoscopy exam and up to the End of Treatment Phase as specified in 6.8 below . Colonoscopies performed prior to this window may be considered interim exams, and study treatment may continue.

*6.5 RAND SF-36v2 Health Survey*

In addition to at enrollment, subjects will also be asked to complete an SF-36v2 health survey two additional times during the study--at the end of year 2 and at the time of the three-year or five-year follow-up colonoscopy exam. This 36-item self-administered questionnaire was constructed to survey health status in the Medical Outcomes Study. It was designed for use in clinical practice and research and has been extensively tested and validated. It assesses eight different health concepts: 1) limitations in physical activities because of health problems; 2) limitations in social activities because of physical or emotional problems; 3) limitations in usual role activities because of physical health problems; 4) limitations in usual role activities because of emotional problems; 5) general mental health (psychological distress and well-being); 6) bodily pain; 7) vitality (energy and fatigue); and 8) general health perceptions.

*6.6 End of Treatment Visit*

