***7.0 Clinical Procedures – Endoscopy***

The endpoint of the study will be new adenomas detected on follow-up colonoscopy. Colonoscopic visualization of the entire large bowel will be performed in each subject approximately 3 or 5 years after the qualifying colonoscopy, as set out before randomization by each patient's clinician.

*7.1 Overview of Procedure*

The coordinator at each Study Center will provide study colonoscopy guidelines to the endoscopist prior to each study exam. Participants will undergo pre-colonoscopy bowel preparation using a standard oral lavage or phospha-soda bowel cleansing preparation, according to the preference of the local study colonoscopist. On the day of the examination each subject will be asked to sign a routine informed consent document for the procedure as required by each institution. Prior to colonoscopy, each subject may receive intravenous medication to achieve desired conscious sedation following the usual practice of the endoscopist performing the procedure. Continuous monitoring of the patient will be carried out by the endoscopy unit nursing personnel before, during, and after the procedure until adequate recovery, according to the standards and practice protocols of the endoscopy unit.

Colonoscopy to the cecum will be performed using standard techniques. The entire colonic mucosa will be carefully examined during withdrawal of the instrument. Detected polypoid lesions will be sized in comparison to open biopsy forceps and then resected using standard biopsy forceps or snare techniques, avoiding cautery if possible. The location of each lesion will be recorded by segment of the colon and centimeters from the anus, and will be submitted to the local pathology laboratory in a separate specimen bottle. Colonoscopic findings will be recorded on the colonoscopy/surgery reporting form immediately after the procedure. If at colonoscopy the preparation is judged to be inadequate, or if the colonoscopy is incomplete for other reasons, a second colonoscopy should immediately be scheduled.

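### The AGI case definition in the Colds and Flu study does not exclude bowel-preparation days, so the exploratory AGI rate ratio is pulled towards 1 by an amount the protocol does not let one determine

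*Protocol*

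**What the plan says.** All references are to the Protocol.

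- **Case definition (10.8.4).** AGI is "either 1) vomiting or watery diarrhea; or 2) nausea or soft diarrhea with abdominal cramps". Nothing is said about cause or procedures. For counting days of illness, the section says the case definitions are applied strictly.
- **Episode rule (10.8.4).** "our definition of an episode of illness requires 6 symptom-free days before a subsequent episode will be said to have occurred".
- **Hypothesis (10.8.2).** Listed as exploratory: "Supplementation with vitamin D3 (1000 IU/day) reduces both the number of episodes of AGI and the days affected by that illness". Unlike the URTI primary hypotheses and the ILI hypothesis, it is not limited to winter.
- **Diaries (6.2).** "Subjects will be asked to complete up to eighteen monthly questionnaires". Also: "We will continue to collect up to five additional questionnaires (not to exceed a total of eighteen) after the completion of the treatment phase".
- **Colonoscopy (6.4, 7.1).** Section 6.4 speaks of the "follow up colonoscopy, which results in the end of the treatment phase of the study for this subject". Section 7.1 says: "Participants will undergo pre-colonoscopy bowel preparation using a standard oral lavage or phospha-soda bowel cleansing preparation". An inadequate or incomplete examination leads to a second one.
- **Model (10.8.4).** Poisson regression by randomized assignment. Over- or under-dispersion is tested, and robust standard errors are used if the test is significant.

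**The concern.** Purgative diarrhea meets the AGI definition as written. A diary that runs across the end of treatment will normally include the preparation that precedes the colonoscopy. Section 10.8 contains no exclusion, and neither do the questionnaire rules in 6.2.

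Preparation happens whichever vitamin D group a person is in. It therefore adds roughly the same count to both groups. An equal addition to the numerator and denominator of a rate ratio moves it towards 1, and it overstates the AGI rate and the number of illness days that would be reported. What is at stake is the size of the estimated AGI effect and the descriptive rates.

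Elsewhere the protocol does guard against preparation. Section 6.3 prefers that the final blood draw not follow it, and the biomarker study in 10.4 takes biopsies without it and specifies the type used at colonoscopy. The AGI outcome, which preparation affects most directly, has no such guard.

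**Working it through.** The protocol states no AGI rate, AGI power or AGI sample size, so there is no AGI figure to reproduce.

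**Inputs**
- Diary sample: "approximately 800 subjects enrolled in our clinical trial of vitamin D and calcium" (10.8.2). Assumed split: 400 with and 400 without vitamin D.
- True rate ratio (RR) 0.70: borrowed from the URTI statement in 10.8.5; an assumption for AGI.
- Genuine AGI episodes per person over the diary, b: not given; 0.3, 0.6 and 1.0 tried, Poisson distributed.
- Share of participants whose diary contains one preparation, s: not given; 0, 0.5 and 1 tried. The six-day rule means one preparation adds at most one episode.
- Two-sided alpha 0.05: stated in 13.5 for the main trial, assumed here.

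**Step 1, attenuation.** Group means are m0 = b + s and m1 = 0.7b + s, so the expected RR is m1/m0.
- b = 0.6, s = 0.5: 0.92/1.10 = 0.84. Preparation is 0.5/1.1 = 45% of control-group episodes.
- b = 0.6, s = 1: 1.42/1.60 = 0.89. Preparation is 1/1.6 = 62%.

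**Step 2, power.** At most one preparation per person is a yes/no count. Its variance is s(1 − s), not s, and is zero when everyone has one. So v0 = b + s(1 − s) and v1 = 0.7b + s(1 − s). The robust standard error of ln RR is √[v0/(400·m0²) + v1/(400·m1²)], and power = Φ(|ln RR|/SE − 1.96).
- b = 0.6, s = 0: SE = √(1/240 + 1/168) = 0.1006; 0.3567/0.1006 = 3.55; power 0.94.
- b = 0.6, s = 0.5: v0 = 0.85, v1 = 0.67, SE = 0.0611; 0.1787/0.0611 = 2.92; power 0.83.
- b = 0.6, s = 1: v0 = 0.60, v1 = 0.42, SE = 0.0333; 0.1193/0.0333 = 3.59; power 0.95.

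| b | s | Expected RR | Power, robust SE | Power if Poisson variance were kept |
|---|---|---|---|---|
| 0.3 | 0 | 0.70 | 0.71 | 0.71 |
| 0.3 | 0.5 | 0.89 | 0.43 | 0.31 |
| 0.3 | 1 | 0.93 | 0.72 | 0.20 |
| 0.6 | 0 | 0.70 | 0.94 | 0.94 |
| 0.6 | 0.5 | 0.84 | 0.83 | 0.72 |
| 0.6 | 1 | 0.89 | 0.95 | 0.54 |
| 1.0 | 0 | 0.70 | >0.99 | >0.99 |
| 1.0 | 0.5 | 0.80 | 0.98 | 0.95 |
| 1.0 | 1 | 0.85 | >0.99 | 0.88 |

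A simulation of the protocol's sequence (chi-squared dispersion test, then robust errors if significant) gave 0.84 for b = 0.6, s = 0.5 and 0.95 for b = 0.6, s = 1. Under-dispersion was flagged in at least 98% of runs in every case checked at s = 0.5 or 1. The robust column is therefore the one that applies.

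**Step 3, a wider range.** Take an 18-month diary, a true RR of 0.80, 0.3 to 1.5 genuine episodes per person-year and s of 0.3 to 1. The ends of the range are:
- 1.5 per year, s = 0.3: b = 2.25, RR = (1.80 + 0.3)/2.55 = 0.82; preparation is 12% of control-group episodes.
- 0.3 per year, s = 1: b = 0.45, RR = (0.36 + 1)/1.45 = 0.94; preparation is 69%.

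**Step 4, days of illness.** Assume 2.5 days per genuine episode, a one-day preparation, 18 months and a true RR of 0.80.
- 0.3 per year, s = 1: genuine days 0.3 × 1.5 × 2.5 = 1.125; preparation share 1/2.125 = 47%; RR (0.90 + 1)/2.125 = 0.89.
- 1.0 per year, s = 0.3: genuine days 3.75; share 0.3/4.05 = 7%; RR 3.30/4.05 = 0.81.

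**The case against.** A reader might infer that preparation episodes swamp the AGI comparison. The documents do not support that. One colonoscopy per participant is planned, and 6.4 discourages extra examinations. Diaries are voluntary and number at most eighteen, and they may be finished before the colonoscopy. Section 6.8 also ends treatment on a calendar date for those not yet finished, so a diary that runs past treatment need not contain a preparation. The dilution runs from slight to large depending on two quantities the protocol does not give.

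A reader might also infer a collapse in power, for example from 0.94 to 0.54 when every diary contains a preparation. That figure treats a constant as though it varied like a Poisson count. Under the dispersion test and robust errors of 10.8.4, no power is lost in that case. Robust errors do not repair the estimate, however: the RR stays at 0.89.

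Third, AGI is exploratory in 10.8.2 and belongs to an ancillary study. This limits the weight of the point. Section 10.8.4 does blur that status by naming episodes and days of each type of illness as primary end points.

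Last, the rule might sit in diary instructions or an analysis plan not shown here. Section 6.2 mentions relevant diagnoses and medications taken for symptoms, but not bowel preparation. That possibility keeps the point small. It does not remove it, because the protocol itself fixes the definition, the episode rule and a worked example of day counting, and as written these count preparation as illness.

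**Conclusion.** The point stands as a minor one. As written, the AGI definition counts bowel-preparation diarrhea as illness whenever a diary covers the colonoscopy. This inflates AGI episodes and days in both vitamin D groups and attenuates the AGI rate ratio.

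The amount cannot be determined from the protocol. With 400 per group, 0.6 genuine Poisson episodes per person and a true RR of 0.70, the expected RR is 0.84 at half overlap and 0.89 at full overlap. The power loss arises at partial overlap and is moderate in that example, 0.94 to about 0.83. It is larger if AGI is rarer (0.71 to 0.43 at 0.3 episodes) and negligible at 1.0. These power figures assume that genuine episodes are not themselves over-dispersed.

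The bias is towards no effect and independent of assignment, so it creates no false positive. The URTI and ILI definitions contain no bowel symptoms, and the adenoma analysis does not use the diaries. All three are unaffected.

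**What to change.** Add to 10.8.4, before unblinding: days from the start of bowel preparation through the day after any colonoscopy are excluded from AGI symptom days, from AGI episodes and from AGI person-time, using the recorded colonoscopy dates. Apply this to repeat and interim examinations as well as the scheduled one, and say how excluded days count towards the six symptom-free days.

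With those days removed s = 0, so the expected RR equals the true RR. The cost is one sentence, a date filter and a few diary days per person. No new data are needed.
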